#### Secondary outcomes

Intrapartum stillbirth except deaths due to congenital anomaliesNeonatal deaths up to 28 days after birth except deaths due to congenital anomaliesModerate or severe encephalopathyAdmission to neonatal unit within 48 h of birth for ≥ 48 h with evidence of feeding difficulties, respiratory illness or encephalopathy (where there is evidence of compromise at birth)Admission to a higher level of careApgar score <4 at 5 minThe distribution of cord blood gas data for cord artery pHMetabolic acidosis (defined as cord artery pH <7.05 and base deficit in extracellular fluid ≥ 12 mmol/l)Resuscitation interventionsSeizuresDestination immediately after birthLength of hospital stay

Health and development outcomes at 24 months (for all infants with trial primary outcome and a further subset of 7000 babies):▪ Non-verbal Cognition Scale (PARCA-R)▪ Vocabulary Sub-scale (PARCA-R)▪ Vocabulary Sub-scale (PARCA-R)▪ Sentence Complexity Sub-scale (PARCA-R)▪ Late deaths up to 24 months (after the neonatal period)▪ Major disability and non-major disability at 2 years▪ Cerebral palsy▪ Breast feeding (collected at 12 and 24 months)

MaternalMode of deliveryOperative intervention (caesarean section and instrumental delivery) for (i) fetal indication, or (ii) failure to progress, or (iii) combination of fetal distress and failure to progress, or (iv) other reason.Grade of Caesarean sectionEpisiotomyAny episode of fetal blood samplingLength of (i) first stage, (ii) second stage and (iii) total length of labour from trial entryDestination immediately after birthAdmission to a higher level of care

#### Quality of care

All babies with an adverse outcome (trial primary outcome plus cord-artery pH <7.05 with base deficit ≥ 12 mmol/l) and all neonatal deaths and intrapartum stillbirths will have their care in labour assessed to see if it was suboptimal. All cases of adverse neonatal outcome (primary outcome plus cord-artery pH <7.05 with base deficit ≥ 12 mmol/l) will undergo panel review similar to that undertaken by CEMACH [16]. Intrapartum notes will be copied and anonymised, and all references to trial allocation will remain. These notes will then be examined by a panel of experienced obstetricians, midwives and neonatologists to identify if there was suboptimal care, particularly in relation to interpretation of the CTG and actions which flow from any identification of CTG abnormalities. The panels will also seek to identify cases with clear evidence of suboptimal care, where the care could be considered negligent in the event of litigation. This information will be important for evaluating whether the decision-support software decreases the risk of suboptimal care in labour; it will also be useful in the economic modelling, which will seek to explore the effect that such an intervention may have on litigation in obstetrics.

#### Process outcomes

It is important to collect and analyse process outcomes in this trial, as a failure to detect differences in clinical or quality of care outcomes between the two randomised groups may be due to poor compliance with the alerts of the system, rather than that the system did not correctly identify abnormalities with the CTG. In addition, as the trial allocation is not masked, it will be important to measure any change that results from clinicians being aware of whether the decision-support system is in operation or not. The following outcomes will therefore be measured to assess this:Proportion of women with a CTG abnormality (as identified by the study software)Number of CTG abnormalities identified in the two arms (as identified by the study software)Time taken between alerts and delivery. This can be achieved in the ‘no decision-support’ arm by using the decision-support software to analyse the CTG trace after the trial is over and using this to determine when the alert would have occurred.Number of routine measurements recorded during labour, including the number of vaginal examinations, use of epidural analgesia, use of labour augmentation and presence of meconium.Number of thumb entries per hour from time of trial entry to first yellow level of concern or until fully dilated*These are proxy measures to assess presence of a health professional in the delivery room during the labour which will allow us to quantify any important differences between the groups with respect to support offered to women during labour. Although unlikely, knowledge of the trial allocation may result in less frequent contact with the woman allocated ‘decision-support’ in labour. Less frequent contact will result in a lower number of these process measures.*

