### Clinical management

The Guardian system will usually be used by all women in labour in the participating centres. It is only the decision-support software, which runs on this system, that is being tested in this trial.

The clinical management of women participating in this trial will remain unaltered by their participation, apart from the relatively uncommon circumstances when abnormalities of the CTG prompt the system in the ‘decision-support’ arm of the trial to issue a series of alerts or alarms, which will increase in urgency with the severity of the abnormality (See Fig. 2).

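### The number of vaginal examinations is counted past the first alert, which only one arm receives live, so a lower or equal count cannot be read simply as less or equal staff contact

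*Protocol article*

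**What the plan says.** The Process outcomes section lists two kinds of measure that serve as contact proxies.

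- Routine measurements: "Number of routine measurements recorded during labour, including the number of vaginal examinations, use of epidural analgesia, use of labour augmentation and presence of meconium". No end point at the first alert is given and no rate per hour.
- Thumb entries: "Number of thumb entries per hour from time of trial entry to first yellow level of concern or until fully dilated".

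The note beneath the list gives their purpose: "These are proxy measures to assess presence of a health professional in the delivery room during the labour". It names the worry, that "knowledge of the trial allocation may result in less frequent contact with the woman allocated ‘decision-support’ in labour", and then gives one reading rule for the whole set: "Less frequent contact will result in a lower number of these process measures".

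The Clinical management section says that management is unaltered by participation, "apart from the relatively uncommon circumstances when abnormalities of the CTG prompt the system in the ‘decision-support’ arm of the trial to issue" alerts or alarms. The Research objectives include prompter action on significant heart rate abnormalities. The Planned interventions section explains that clinicians are deliberately not masked and gives changes in midwifery presence as an example of an effect of knowing the allocation.

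**The concern.** The two proxies have different counting windows but share one interpretation. Ending the thumb-entry rate at the first yellow level keeps activity that follows an alert out of that measure. The examination count has no matching boundary, so in the decision-support arm it adds together two things: any change in background contact caused by staff knowing the allocation, and whatever happens after a live alert.

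The second part can move the count either way. If an alert brings someone to examine the woman, the count rises. If it brings delivery forward, labour is shorter and a count that is not expressed per hour falls. The first could partly mask a real fall in contact. The second could look like a fall when background contact had not changed.

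At stake is the protocol's own check on a side effect that it takes seriously enough to measure. An equal examination count could be reported as reassurance, or a lower one as neglect, when the count alone supports neither reading. Starting the count at trial entry would not cure this. Dividing by hours would deal with the shorter labour but not with the examinations that follow alerts.

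**Working it through.** The protocol gives no expected examination count, alert rate or power for these proxies, so there is no stated figure to reproduce. The check is first a comparison of the text and then an illustration on assumed inputs.

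**Text.**

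| | Thumb entries | Vaginal examinations |
|---|---|---|
| Start | trial entry | not stated (during labour) |
| Stop | first yellow level or full dilatation | none stated |
| Scale | per hour | number |
| Can include activity after a live alert | no | yes, decision-support arm only |
| Reading rule | lower means less contact | the same |

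The rule is sound for the first column. For the second it needs the added assumption that alerts change neither the number of examinations nor the length of labour.

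**Illustration.** Net difference in mean examinations (decision support minus control) = −r·V + f·e, where:

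- V = 4, the usual number of examinations per labour (assumed);
- r = 5%, the fall in background contact (assumed), so r·V = 0.20;
- f = 10% or 29%, the share of women with an alert. Both are assumed. The 29% is the share with an abnormal CTG among 120 controls in a case–control study described under Human error and systems failure. It is not an alert rate for this software;
- e = 0.5 or 1, the examinations per alerted woman over and above what control staff would do for the same trace (assumed).

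Standard error, with SD 2 (assumed) and 23,000 women per arm (Effect size section): 2 × √(2/23,000) = 0.0187.

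| f | e | Net difference | In standard errors |
|---|---|---|---|
| 10% | 0.5 | −0.20 + 0.050 = −0.150 | −8.0 |
| 10% | 1 | −0.20 + 0.100 = −0.100 | −5.4 |
| 29% | 0.5 | −0.20 + 0.145 = −0.055 | −2.9 |
| 29% | 1 | −0.20 + 0.290 = +0.090 | +4.8 |

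In three of the four cases the difference stays negative and detectable, although smaller than the true fall. It changes sign only when the borrowed 29% is combined with a full extra examination each. With r = 10% even that corner stays negative: −0.40 + 0.29 = −0.11, or 5.9 standard errors below zero.

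The fall is fully masked when e = r·V/f. For a 5% fall this is 0.20/0.10 = 2.0 extra examinations per alerted woman if 10% are alerted, and 0.20/0.29 = 0.69 if 29% are. For a 10% fall it is 4.0 and 1.4.

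**The other direction.** Suppose background contact does not change (r = 0) and alerts bring delivery forward so that each alerted woman has one examination fewer (e = −1, assumed). The difference is −0.10 at f = 10% and −0.29 at f = 29%. Under the stated rule this would be read as a 2.5% to 7% fall in contact that did not happen.

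**The case against.** The strongest reply is that the same section already holds the cleaner measure. The thumb-entry rate ends at the first yellow level, so a fall in contact before an alert, or in women who never have one, can show there. This stands. A reader might infer that the safeguard as a whole fails, and the document does not support that: one of two complementary proxies is less clean than the other.

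Second, contact prompted by an alert is still contact. The note speaks of support offered during labour, and a trial meant to reflect ordinary practice has reason to describe care over the whole labour. This also stands. It is a reason to keep the whole-labour count, but not to read it by the pre-alert rule.

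Third, a reader might infer that alerts raise the number of examinations and so hide a fall in contact or reverse its sign. No section says that alerts increase examinations. Control staff also see and act on abnormal traces, so only the net excess counts, and the alert circumstances are called relatively uncommon. The illustration reverses only at one assumed corner. Sign reversal is therefore not a finding.

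Fourth, the argument does not extend to every routine measurement. Epidural use, augmentation and meconium are largely yes/no items, weak as contact measures in any case, and an hourly count of them makes little sense.

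Last, an SAP may set a narrower window. The protocol nevertheless fixes both the open window and the unqualified reading rule, and it is that wording which needs the qualification.

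**Conclusion.** The point holds as a limited one about interpretation. For the number of vaginal examinations, the rule that less contact gives a lower number is unsafe, because the count continues past the first yellow level and live alerts occur in one arm only. The bias may mask a fall in contact or imitate one. Its size cannot be obtained from the document, since it depends on the alert rate, the net extra examinations per alert and the effect of alerts on length of labour, none of which is given. On the assumed inputs with 10% of women alerted, a quarter to a half of a 5% fall is masked and the remainder is detectable. The pre-alert thumb-entry rate is unaffected by this mechanism. The primary outcomes are not touched. This is a minor improvement to a process outcome and not a design error.

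**What to change.** 1. As the contact proxy, also report vaginal examinations per hour from trial entry to the first yellow level, full dilatation or birth, whichever comes first.
2. Derive the first yellow level by the software in the same way in both arms. The Process outcomes section already plans to run the software on control traces after the trial to find when an alert would have occurred.
3. Report examinations after that point separately, as response to alerts.
4. Keep the whole-labour count as a description of total care.
5. Limit the sentence that equates fewer counts with less contact to the pre-alert rates.

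The cost is programming and one edited sentence. No new data collection is needed if the time of each examination is held, which the contemporaneous storage described under Data collection suggests. The downside is fewer events per woman in the shorter window. Women randomised in the second stage, whom the eligibility section allows, contribute no time to it.

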#### Data collection

For all participating women and babies, labour variables and outcomes will be stored automatically and contemporaneously onto the Guardian® system. Data collected via the system will be sent electronically to the trial co-ordinating centre at the UCL Clincial Trials Unit (UCL CTU) in London. Data will be extracted from the notes of babies admitted to the neonatal unit and for all neonatal deaths. It should be noted that not all data fields are collected at every centre. However, where an item is collected these data will be sent to the UCL CTU. The trial is not collecting the reason why continuous EFM is being used, as this is not recorded. All children surviving to be discharged home from hospital following their birth will be ‘flagged’ at the NHS Information Centre for those born in England and Scotland and all deaths occurring after discharge home from hospital will be notified to the trial co-ordinating centre at the UCL CTU. At 2 years after trial entry a sample of 7000 surviving children (3500 in each group) will be followed up at 2 years of age. This sample will be taken from within the sample recruited during the first 2 years of the project so that follow-up of this group can be completed around the time that the trial stops recruiting. As there seems little possibility that the nature of the effect of the intervention will vary over the duration of trial recruitment, this process will be the most efficient use of resources. For children in the follow-up group, their family will be sent a two part parent-completed questionnaire to assess the child’s health, development and well-being. The first part of the questionnaire comprises the PARCA-R, which has been previously validated as a means of assessing neurodevelopment in a trial setting. The second part focuses on general health issues, and has also been used previously [28, 29]. Major disability at 2 years will be assessed by questionnaires sent to the child’s parents and health care professionals. Major disability will be defined according to the criteria set out in the National Perinatal Epidemiology Unit (NPEU) and Oxford Regional Health Authority document and will include any major disability in the following domains: neuromotor function, seizures, auditory function, communication, visual function, cognitive function and other physical disability [30, 31].

#### Health economics

A prospective economic evaluation will be conducted alongside the trial, with the aim of estimating the cost-effectiveness of the intelligent decision-support software. The economic evaluation will be conducted from a health-service perspective. Information on resource utilisation will be collected through the Guardian® system and hospital-patient administration and maternity information systems. Observational research methods may be used to collect additional costs in intrapartum, postpartum or neonatal care. Current UK unit costs will be applied to each resource item to value total resource use in each arm of the trial. A per diem cost for each level of intrapartum, postnatal and neonatal care will be calculated using NHS reference costs where appropriate, or by sending a detailed questionnaire to the finance department of each centre participating in the trial. The unit costs of clinical events that are unique to this trial will be derived from the hospital accounts of the centres participating in the trial, although primary research may also be required. An incremental cost-effectiveness analysis will be performed and primarily expressed in terms of an incremental cost per poor-perinatal-outcome prevented. The primary outcomes of the trial are likely to have longer-term consequences in terms of health status and health-service utilisation over the mother’s and infant’s lifetime. Consequently, two long term economic evaluations are planned, which in the first instance will estimate the cost-effectiveness of the decision-support software when surviving children reach 2 years of age, and in the second instance will incorporate the lifetime cost and health consequences of the mother and child. To inform the long-term economic evaluations, a subsample of 700 healthy infants selected within the first year of recruitment and all babies with the primary trial outcome who survive to hospital discharge and agree to follow-up will be followed up until 2 years of age or until the end of the trial, whichever comes first. Economic questionnaires completed when the infant reaches 1 and 2 years of age will document the health and social care use of the child and mother. Cost data collected until hospital discharge and from the parental questionnaires will be combined with the PARCA-R composite score at 2 years of age to inform the incremental cost per disability free life years gained when surviving children reach 2 years of age [32]. Given the potential long-term sequelae, these data will then be used to extrapolate long-term outcomes and costs over the child’s lifetime, identifying future health care costs and the health status of mothers and infants from literature as well as the application of decision-analytic or markov methods to synthesise information from different sources. This will require modeling longer-term health-service utilisation from literature and also estimating the potential medico-legal claims that result from adverse events during the intrapartum and neonatal periods.

#### Proposed sample size

The proposed sample size is 46,000 births in total.

The following data sources and assumptions have been used in the calculation of the trial sample size:

#### Incidence of intrapartum stillbirth

This has been estimated as 0.35 per 1000 births. This estimate is derived from the following incidence data: 0.51 per 1000 for all gestations (England, Wales and Northern Ireland, 2004) [33]; 0.27 per 1000 for gestation ≥ 37 weeks (Trent Region, 2002) [34]. This trial is restricting eligibility to women over 35 weeks’ gestation; therefore the incidence will be lower than in women of all gestational ages, which includes those with preterm births. However, it will be higher than for women at term. As women being recruited are all judged to require continuous electronic fetal monitoring it can be assumed that the identification of this “risk group” means that these women are at increased risk of adverse outcomes; therefore the incidence may be higher. In addition these estimates use a denominator of all births which includes women having elective caesarean sections who are not at risk of intrapartum stillbirth as they have no “intrapartum” period. Approximately 7 % of women have elective caesarean section and removal of these women will increase the incidence further. An estimate of 0.35 per 1000 births, therefore, appears reasonable.

#### Incidence of neonatal death

This has been estimated as 0.7 per 1000 births. This estimate is derived from the following data: 3.4 per 1000 for all gestations (England, Wales and Northern Ireland, 2004) [33]; 0.89 per 1000 in those with gestation ≥ 37 weeks (Trent Region, 2005) [32]. This trial is restricting eligibility to women 35 weeks’ gestation or over; therefore the incidence will be lower than amongst women of all gestational ages, which includes those with preterm births. However, it will be higher than for women at term. A reasonable estimate of neonatal death for babies 35 weeks’ gestation or over is therefore 1.0 per 1000 births. Using data from the Trent Survey 2005, 30 % of neonatal deaths were due to congenital anomalies. Therefore this rate can be reduced to 0.7 per 1000 births. As women being recruited are all judged to require continuous electronic fetal monitoring it can be assumed that the identification of this “risk group” means that these women are at increased risk of adverse outcomes; therefore the incidence may be higher. An estimate of 0.7 per 1000 births, therefore, appears reasonable.

#### Incidence of severe and moderate neonatal encephalopathy

The best estimate of the incidence of neonatal encephalopathy in babies born 35 weeks’ gestation or over is 1.3 per 1000 (Trent & Northern Region 2002) [35]. However, as above, women being recruited to this trial are all judged to require continuous electronic fetal monitoring which means that they are at increased risk of adverse outcomes; therefore the incidence may be higher.

#### Combined outcomes

Data are available on some combined outcomes. For example, the incidence of intrapartum stillbirth plus deaths on labour ward assumed to be due to intrapartum asphyxia (the incidence of which is much lower than neonatal mortality) plus severe and moderate neonatal encephalopathy was 1.7 per 1000 (95 % CI: 1.5 to 1.9), range 0.8–2.3 (18 hospitals, Trent 2003–4) and 1.9 per 1000 (95 % CI: 1.6 to 2.3), range 0.6–2.3 (12 hospitals, Yorkshire Neonatal Network 2004–5) [35]. This was for babies born at 35 weeks’ gestation or above with the incidence of these outcomes being higher in the larger hospitals, which attract women with more complicated pregnancies.

#### Incidence of primary outcome for INFANT

We have assumed an incidence of the primary outcome of 3 per 1000 births. This has been calculated by summing the rate of intrapartum stillbirth, neonatal death and moderate and severe encephalopathy which gives an incidence of 2.35 per 1000 births. However, added to this figure is mild encephalopathy, which is reported to occur in 1.25 per 1000 births, and other significant morbidity (other admissions to the neonatal unit within 48 h of birth for ≥ 48 h e.g. feeding difficulties, respiratory symptoms, seizures), for which there are no good estimates of incidence. This estimate of 3 per 1000 births errs on the side of caution and an increased incidence of this outcome in the trial will either (a) increase the power of the trial to demonstrate the same effect size, or (b) allow detection of a smaller effect size with the same trial size, or (c) necessitate a smaller trial if the postulated effect size (or larger) is detected.

